### Data collection and patient follow up

Baseline data (on age, sex, performance status (Karnofsky score), American Society of Anesthesiologists physical status, body mass index, malnutrition universal screening tool score (MUST), ERAS mobility scale [31, 32], diabetes mellitus, previous abdominal surgery, preoperative imaging including tumor size and involvement of other organs, preoperative diagnosis, indication for hospitalization, indication for surgery) will be collected before randomization using standardized case report forms. Data on the primary and secondary outcomes will be collected from randomization up to 90 days postoperatively, by the local treating physicians or the trial coordinators using standardized case report forms. The case report forms and the database will be crosschecked with source data by the trial coordinators.

Patients will be asked to complete validated questionnaires (EQ-5D-5 L and QLQ-C30) at 2 weeks, 4 weeks and 12 weeks postoperatively (Fig. 1). One year after surgery, patients will be asked whether they are totally recovered and will be asked to complete questionnaires on quality of life (Euro-QoL 5 health dimensions questionnaire (EQ-5D-5 L) and Quality of life questionnaire including 30 questions (QLQ-C30)), complications and whether they would recommend MIDP or ODP to a friend or family member. Long-term follow-up results of the LEOPARD trial (including complications and quality of life) will be published separately.

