In 2014, the Dutch Pancreatic Cancer Group (DPCG) initiated the longitudinal assessment and realization of minimally invasive pancreatic surgery in The Netherlands (LAELAPS) training program to implement minimally invasive pancreatic surgery in The Netherlands [17]. This program follows the preferred steps of surgical innovation according to the innovation, development, exploration, assessment and long-term study (IDEAL) statement [18–20].

First, a nationwide retrospective analysis on distal pancreatectomy was performed in order to assess the utilization and outcomes of MIDP and ODP [21]. In this retrospective multicenter study in 633 patients, MIDP appeared to be at least non-inferior to ODP, but the nationwide underuse of MIDP (10%) and high conversion rate (38%) revealed clear room for improvement. The subsequent nationwide LAELAPS training program included detailed technique standardization and description, video training and proctoring [17]. In the period after training, there was a sevenfold increase in the use of MIDP, and blood loss and conversion rates decreased even during surgery on more complex tumors, including more pancreatic ductal adenocarcinomas. The 8% conversion rate, 17% Clavien-Dindo grade III or higher complication rate, 6 days hospital stay and 0% 30-day mortality in the period after training were comparable to results from expert centers in the UK and USA [11]. According to the IDEAL framework, a randomized controlled trial should be the next step [18–20]. Accordingly, the aim of the LEOPARD trial is to compare the outcomes, including time to functional recovery, complications, quality of life and costs, after MIDP with ODP within an enhanced recovery setting.

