### Statistical aspects

#### Sample size calculation

The LEOPARD trial is designed as a superiority trial, hypothesizing that the time to functional recovery is significantly shorter after MIDP compared with ODP. Based on the most recently published meta-analysis [11] and Dutch nationwide data, a time to functional recovery of 8 days in the control group (ODP) versus 6 days in the intervention group (MIDP) is expected with a standard deviation of 3 days. The significance level (α) is set at 0.05 and power (1-β) at 80%. The sample size needed in each arm, calculated using the independent samples *t* test, is 36 patients. Including 15% crossover from the MIDP to ODP and a rate of 2% loss to follow up (based on previous studies), a total of 51 patients will be randomized in each group, so a total of 102 patients will be randomized in the LEOPARD trial.

After completion of data collection in the first 75 patients, the data safety monitoring board will assess potential data skewness and homogeneity of variance for time to functional recovery. When a non-parametric test seems indicated for the comparison of MIDP versus ODP on time to functional recovery, the total sample size will become the calculated sample size (102) divided by the asymptomatic relative efficiency parameter of the Mann–Whitney *U* test (0.955). In that case, a total of 108 patients will be randomized in the LEOPARD trial. Procedures performed using the robot DaVinci® Surgical System are allowed in this trial, but will be analyzed separately during the cost analysis.

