#### Statistical analysis

Primary and secondary outcomes will be crosschecked with data from primary sources and a blinded adjudication committee will check them against the definitions, which were established before the start of this trial. Categorical variables will be compared using the chi-square or Fisher’s exact test as appropriate, and values will be expressed as proportions. The distribution of continuous variables will be determined using visual inspection and the Kolmogorov-Smirnov test.

For comparison of normally distributed continuous variables the independent samples *t* test will be used and values will be expressed as means with standard deviations. Continuous non-normally distributed variables will be compared using the Mann–Whitney *U* test and values will be expressed as medians with interquartile ranges. Measures of association will be expressed as relative risks with 95% confidence intervals. A difference with a two-tailed *P*-value <0.05 will be considered statistically significant.

Analyses will be performed based on intention-to-treat principles, meaning that converted MIDP will be assessed in the MIDP group. A multivariable linear regression model will be used to assess potential differences between groups in the primary outcome in the presence of potentially confounding factors. Linear mixed modeling will be applied to estimate differences between groups in successive EQ-5D-5 L and QLQ-C30 assessments over time. For exploratory purposes a secondary analysis will be performed comparing outcomes in patients with malignant versus non-malignant disease, comparing completed MIDP (i.e. no conversion) versus ODP and comparing time to functional recovery between MIDP and ODP in patients with complications (Clavien-Dindo score ≥ III) and without complications.

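### The article lists no quality-of-life questionnaire before surgery or in the first two weeks, so early differences cannot be seen and the mixed model has no baseline score (confirm against Figure 1)

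*Protocol article*

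**What the plan says.** The Background of the protocol article sets the aim as to "compare the outcomes, including time to functional recovery, complications, quality of life and costs, after MIDP with ODP within an enhanced recovery setting". Quality of life is thus a named objective, and it appears again under Secondary outcomes.

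The measurement schedule is under Data collection and patient follow up: "Patients will be asked to complete validated questionnaires (EQ-5D-5 L and QLQ-C30) at 2 weeks, 4 weeks and 12 weeks postoperatively". It continues: "One year after surgery, patients will be asked whether they are totally recovered and will be asked to complete questionnaires on quality of life". The schedule sentence refers to Figure 1, which is missing from the text at hand.

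The same section itemises the baseline data. The list opens with "Baseline data (on age, sex, performance status (Karnofsky score), American Society of Anesthesiologists physical status, body mass index" and closes with "preoperative diagnosis, indication for hospitalization, indication for surgery) will be collected before randomization using standardized case report forms". Neither EQ-5D-5L nor QLQ-C30 is in it. The nearest items are the Karnofsky score and the ERAS mobility scale.

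Under Statistical analysis the planned method is: "Linear mixed modeling will be applied to estimate differences between groups in successive EQ-5D-5 L and QLQ-C30 assessments over time". The planning assumption under Sample size calculation reads: "a time to functional recovery of 8 days in the control group (ODP) versus 6 days in the intervention group (MIDP) is expected". The SD used there is 3 days.

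**The concern.** Two things follow from the schedule as printed.

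- **Timing.** The first form comes at day 14. Any difference in how patients feel during the first two weeks goes unrecorded. This includes the days in which the plan expects recovery times to separate.
- **Baseline.** The mixed model has only post-treatment values. Patients range from symptomatic benign disease to cancer, so preoperative quality of life plausibly varies widely. Without a preoperative score, that variation stays in the residual, a chance imbalance in quality of life itself between arms of about 51 cannot be checked directly, and return to the preoperative level cannot be reported.

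At stake are the scope and precision of a secondary objective. The primary outcome is not affected.

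**Working it through.** **Inputs.** From Sample size calculation: means 8 (open) and 6 (minimally invasive) days, SD 3, alpha 0.05, power 80%, crossover 15%, loss to follow-up 2%, 51 per arm. Two-sided testing is from Statistical analysis. The first questionnaire at day 14 is from Data collection and patient follow up. The figure of 78 of 102 randomized is from Trial status.

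**1. The plan's own figure.** n per arm = 2 × (1.96 + 0.8416)² × 3² / 2² = 35.3, rounded up to 36. Inflation: 36 / (0.85² × 0.98) = 50.8, so 51 per arm and 102 in total. Both stated figures reproduce, so the inputs are being read as the plan meant them.

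**2. Share functionally recovered by day 14**

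- Normal, open: Φ((14 − 8)/3) = Φ(2.00) = 97.7%.
- Normal, minimally invasive: Φ((14 − 6)/3) = Φ(2.67) = 99.6%.
- Pooled 1:1: (97.7 + 99.6)/2 = 98.7%.

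The plan itself allows for skewness, so two right-skewed distributions with the same mean m and SD 3 were tried:

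- Log-normal, with log-scale variance ln(1 + 9/m²): 95.8% open, 97.9% minimally invasive.
- Gamma, with shape (m/3)² and scale 9/m: 96.1% and 98.3%.

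With an SD of 5 days (an assumption, not in the document), the shares are 88.5% to 89.6% open and 93.7% to 94.5% minimally invasive across normal and log-normal forms.

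**3. What a baseline score could be worth.** The document gives no baseline-to-follow-up correlation r, so a range is assumed. For one follow-up time, adjustment multiplies the variance by 1 − r². With 51 × 0.98 ≈ 50 per arm, the standardized difference detectable with 80% power is 2.8016 × √(2/50 × (1 − r²)).

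| Assumed r | Variance cut | Detectable difference (SD units) |
|---|---|---|
| no baseline | none | 0.56 |
| 0.3 | 9% | 0.53 |
| 0.5 | 25% | 0.49 |
| 0.7 | 49% | 0.40 |

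This shows what a baseline for every patient would give. It is not what can still be obtained.

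**4. What can still be obtained.** 102 − 78 = 24 patients remain, or 108 − 78 = 30 if the Mann–Whitney enlargement is triggered. That is 24/102 = 24% or 30/108 = 28% of the trial. Split evenly, 12 to 15 per arm would have an early form. The detectable difference at that time point alone is 2.8016 × √(2/12) = 1.14 to 2.8016 × √(2/15) = 1.02 SD units, so it would be descriptive only.

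**The case against.** The strongest reply has five parts.

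- **Figure 1 may show a baseline form.** Its caption defines both instruments, the printed times are expressly postoperative ones, and the baseline list concerns case report forms, not patient-completed questionnaires. The article also condenses a fuller protocol. This stands: the text supports only that none is listed. A reader might infer that no baseline was taken, but the document does not establish that.
- **Functional recovery is not quality of life.** General treatment regimen equates it with medical readiness for discharge, and its criteria can be met by a patient still on oral analgesics and eating half of what is required. This also stands. A reader might infer that the schedule misses the period in which the quality-of-life effect is expected. No section says when that effect is expected, and the 6-versus-8-day figures belong to another endpoint. The arms may still differ in quality of life after day 14.
- **Randomization protects the comparison.** Comparisons at 2, 4 and 12 weeks are valid without a baseline. Stratification by malignant versus non-malignant disease, and the Karnofsky score taken before randomization, partly cover imbalance. This stands, though these are proxies.
- **The precision gain is assumed.** The correlations are not from the document, and the formula is for one follow-up, not for a repeated-measures model. This stands, so the table above is illustrative.
- **It is late.** About three quarters of patients were already randomized at submission. A baseline entered as an ordinary covariate could, under complete-case handling, shrink the analysis to the few who have it. This stands and shapes the remedy.

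None of these removes the core point. A schedule with stated times is a design decision, not a detail left to an analysis plan, and as printed it has nothing before day 14.

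**Conclusion.** The point holds as a cheap improvement to a secondary objective. As printed, the schedule cannot show any quality-of-life difference in the first two weeks. By the end of that period 97.7% and 99.6% of patients are functionally recovered under normality, and about 96% to 98% with right skew. The mixed model has no pre-treatment score for precision or for examining chance imbalance in quality of life.

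This rests on the planned means and SD being roughly right and on Figure 1 and the full protocol not listing a preoperative or earlier form. If either does, the corresponding part falls away.

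A reader might go further and expect a finding of no difference produced by the schedule. The document does not support that: a null result is a risk, not shown to be likely.

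**What to change.** 1. Check Figure 1 and the full protocol. If a preoperative questionnaire was collected, say so and use it as in step 3.
2. If not, for all patients still to be enrolled, add EQ-5D-5L and QLQ-C30 before randomization and one short EQ-5D-5L on a fixed early in-hospital day. Keep the same day in both arms, so that timing does not depend on speed of recovery.
3. Enter any baseline score as a time point in the linear mixed model, with a common baseline mean across arms. Patients without it are then kept.
4. Adjust the model for the malignant/non-malignant stratum and the Karnofsky score, which the plan already collects for every patient before randomization.
5. For patients without the early form, limit the quality-of-life conclusion to the period from 2 weeks onward.

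**Cost.** A small questionnaire burden and a minor amendment. The gain from new forms is partial, since they reach only 24 to 30 patients. Steps 4 and 5 apply to everyone and need no new data.

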### Definitions

The distal pancreas is defined as the proportion of the pancreas located at the left of the portomesenteric vein. Complications are classified using the Clavien-Dindo score [33]. Major complications are defined as a Clavien-Dindo score III or higher. Postoperative pancreatic fistula [34], delayed gastric emptying [35] and post-pancreatectomy hemorrhage [36] are classified using the International Study Group on Pancreatic Fistula (ISGPF) and the International Study Group on Pancreatic Surgery (ISGPS) definitions, respectively. Surgical site infection is classified according to the Centers for Disease Control and Prevention definition [37]. In the case of malignant pancreatic disease, resection margins, including transection and circumferential margins, are classified by a margin to tumor distance ≥1 mm (R0), a margin to tumor distance <1 mm (R1) or a macroscopically positive margin (R2) [38]. Tumor, node, metastases (TNM) status is classified according to the American Joint Committee on Cancer (AJCC) classification (7^th^ edition).

### Quality and safety

Surgeons will only be allowed to participate in the LEOPARD trial when they have completed LAELAPS training in MIDP [17] and have performed >50 advanced minimally invasive advanced gastrointestinal procedures, >20 distal pancreatectomies (either MIDP or ODP) and >5 MIDPs. An advanced minimally invasive gastrointestinal procedure is defined as any minimally invasive gastrointestinal procedure beyond diagnostic laparoscopy, cholecystectomy and appendectomy. If surgeons do not meet all of the predefined criteria, they will be assisted by an experienced MIDP surgeon (defined as having performed >20 MIDPs) as often as necessary until the criteria are met. Each participating surgeon will record a video of the first MIDP performed in the trial. This video will be shortened to enable efficient scoring of the operator’s skills and scored by an expert MIDP surgeon, who will score the video (blinded for the surgeon and clinical outcomes) using the method described by Birkmeyer et al. [39]. The expert surgeon will assess each video in five domains of technical skills (gentleness, tissue exposure, instrument handling, time and motion and flow of the operation). Each domain will be rated on a scale of 1–5, where 1 indicates the skill expected of a general surgical resident and 5 the skill of a master surgeon in the procedure of minimally invasive distal pancreatectomy.

All adverse events reported spontaneously by the patient or observed by the investigator or his staff will be recorded up to 90 days postoperatively. Serious adverse events occurring within 90 days after treatment will be recorded. Only serious adverse events from a predefined list will be reported through a Web portal to the central committee on research involving human subjects (in Dutch: central *Commissie Mensgebonden Onderzoek*) and the accredited institutional review board (www.toetsingonline.nl). This includes serious adverse events that necessitate intensive care unit admission, necessitate surgical intervention, necessitate readmission or result in mortality (for any reason). The remaining events are recorded in a yearly overview list. An independent data safety monitoring board will meet to investigate the safety parameters after every 25 included patients. This data safety monitoring board comprises one independent statistician/epidemiologist (Chair), one independent gastroenterologist and one independent surgeon. The result(s) of the data safety monitoring board meeting will be sent to all participating physicians involved in this trial. Furthermore, the result of the meeting will be relayed to the trial steering committee. The advice of the data safety monitoring board will only be sent to the sponsor of the trial.

### Statistical aspects

#### Sample size calculation

The LEOPARD trial is designed as a superiority trial, hypothesizing that the time to functional recovery is significantly shorter after MIDP compared with ODP. Based on the most recently published meta-analysis [11] and Dutch nationwide data, a time to functional recovery of 8 days in the control group (ODP) versus 6 days in the intervention group (MIDP) is expected with a standard deviation of 3 days. The significance level (α) is set at 0.05 and power (1-β) at 80%. The sample size needed in each arm, calculated using the independent samples *t* test, is 36 patients. Including 15% crossover from the MIDP to ODP and a rate of 2% loss to follow up (based on previous studies), a total of 51 patients will be randomized in each group, so a total of 102 patients will be randomized in the LEOPARD trial.

After completion of data collection in the first 75 patients, the data safety monitoring board will assess potential data skewness and homogeneity of variance for time to functional recovery. When a non-parametric test seems indicated for the comparison of MIDP versus ODP on time to functional recovery, the total sample size will become the calculated sample size (102) divided by the asymptomatic relative efficiency parameter of the Mann–Whitney *U* test (0.955). In that case, a total of 108 patients will be randomized in the LEOPARD trial. Procedures performed using the robot DaVinci® Surgical System are allowed in this trial, but will be analyzed separately during the cost analysis.

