### Primary outcome

The primary outcome is time to functional recovery (days). Functional recovery will be daily assessed by the nurses, ward physicians and the trial coordinators and is reached when all of the following criteria are met:Adequate pain control with oral analgesia onlyRestoration of mobility to an independent level (or to preoperative level if previously impaired)Ability to maintain sufficient caloric intake (minimum of 50% required calories); absence of intravenous fluid administrationNo signs of active abdominal infection (in the case of abdominal infection this item is met when serum C-reactive protein is below 150 mg/L and the patient has no fever)

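### The primary test is left to two data-driven checks with no order of precedence, and the fallback of 108 patients uses a Mann-Whitney efficiency that belongs to normal data

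*Protocol article*

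**What the plan says.** The protocol article sizes the trial on a t test (Sample size calculation). It expects mean recovery times of 8 days (open) and 6 days (minimally invasive), a difference that "is expected with a standard deviation of 3 days". The significance level "is set at 0.05 and power (1-β) at 80" percent. This gives 36 per arm, raised for 15% crossover and 2% loss to 51 per arm, 102 in total.

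The same section adds a check during the trial: "After completion of data collection in the first 75 patients, the data safety monitoring board will assess potential data skewness" and also homogeneity of variance. No test or threshold is given. If a rank-based comparison then appears warranted, "the total sample size will become the calculated sample size (102) divided by the asymptomatic relative efficiency parameter" of the Mann-Whitney test, stated as 0.955, and 108 patients are randomized. (The word before relative efficiency is a slip for asymptotic and has no consequence.)

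The Statistical analysis section has a second check, for all continuous variables: "The distribution of continuous variables will be determined using visual inspection and the Kolmogorov-Smirnov test". Variables judged normal go to the t test and the others to Mann-Whitney. Neither section names one test for the primary outcome or says which check governs if they differ.

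**The concern.** There are two faults.

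First, the confirmatory test depends on the observed data through two checks. They differ in criterion (skewness and variance, against visual inspection and Kolmogorov-Smirnov) and in timing (75 patients, against the final data). If the first points to a rank test and the second does not, the trial has been enlarged for a test that it does not use. In the reverse case, Mann-Whitney is used without the increase that the plan itself considers necessary for it.

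Second, the fallback size uses an efficiency whose condition has just been judged not to hold. The value 0.955 compares Mann-Whitney with the t test for a shift between normal distributions of equal variance. The rule applies when the data look skewed or the variances unequal.

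At stake are a pre-specified primary analysis, and a sample-size rule that delivers what it is meant to deliver.

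**Working it through.** **Inputs.** From the article: means 8 and 6 days, SD 3, α 0.05 two-sided, power 80%, 15% crossover, 2% loss, 102 patients, efficiency 0.955, fallback 108. Assumed: the shape of recovery times, taken as normal, gamma or lognormal with those means and SD 3.

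**The plan's own figures.**
- Per arm: 2 × (1.960 + 0.842)² × 3² / 2² = 2 × 7.85 × 2.25 = 35.3, so 36. (The exact t-test solution is 36.3; the difference is immaterial here.)
- Inflated: 36 / (0.85² × 0.98) = 36 / 0.708 = 50.8, so 51 per arm and 102 in total.
- Fallback: 102 / 0.955 = 106.8. Rounded up per arm, 51 / 0.955 = 53.4, so 54 per arm and 108 in total.

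All stated figures reproduce.

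**Where 0.955 comes from.** For a shift between two distributions of the same shape f, the efficiency of Mann-Whitney relative to the t test is 12 σ² (∫f²)². For a normal density ∫f² = 1 / (2σ√π), so the efficiency is 3/π = 0.955.

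**The same formula for right-skewed shapes with SD 3**, where 12 σ² = 108:

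| Shape | Mean | ∫f² | Efficiency |
|---|---|---|---|
| Gamma | 8 | 0.0994 | 1.07 |
| Gamma | 6 | 0.1042 | 1.17 |
| Lognormal | 8 | 0.1073 | 1.24 |
| Lognormal | 6 | 0.1177 | 1.50 |

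All exceed 1, so no increase over 102 is called for. The lowest value that the efficiency can take for any shape in the shift model is 0.864: 102 / 0.864 = 118.1, or 120 with equal arms (51 / 0.864 = 59.03, so 60 each).

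**Power.** These shapes with equal SD are not exact shifts, so the result was checked by simulation with 50 per arm, 15% of the minimally invasive arm drawn from the open-surgery distribution, and SD 3:

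| Shape | t test | Mann-Whitney |
|---|---|---|
| Normal | about 79% | about 78% |
| Gamma | about 79% | about 85% |
| Lognormal | about 79% | about 89% |

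The two tests disagreed on significance in about 5% of trials with normal data, rising to about 11% with lognormal data.

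**How often the two checks could disagree.** The article gives no thresholds, so this is illustrative. The first check was taken as a skewness or Levene test at 5% on 75 patients. The second was Kolmogorov-Smirnov at 5% on the pooled 102 values, either plain or with the Lilliefors correction for estimated parameters.

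| Shape | First check flags | Plain K-S flags | Lilliefors flags | Checks disagree (plain / Lilliefors) |
|---|---|---|---|---|
| Gamma | 77% | 2% | 45% | 75% / 43% |
| Lognormal | 94% | 12% | 72% | 81% / 26% |

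The article does not say which form of Kolmogorov-Smirnov is meant, and the choice changes the answer considerably.

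**The case against.** The strongest defence is that little harm follows. The only consequence stated for the check at 75 patients is the number randomized, and the Statistical analysis section governs the test. On that reading there is one test selection, and an increase of at most 6 patients that errs on the generous side for right-skewed data. Choosing the test from the data also costs little in type I error: selection by Kolmogorov-Smirnov or Lilliefors followed by the chosen test gave 5.0% to 6.2% under the null, and always taking the smaller p-value gave 6.3% to 7.2%. Visual inspection would temper a purely mechanical choice.

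Most of this stands and limits the severity. It does not remove the point. The trigger for 108 is a judgement about which primary test is warranted, so the two sections answer the same question by different rules without saying which prevails. Nor is this detail left to an analysis plan that is not shown: the article states both rules and the efficiency figure.

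A reader might infer more than the documents support:
- **That skewness takes the t test well below 80% power.** At SD 3 it stays at about 79% for all three shapes. A fall needs a larger SD. Suppose the 17% with major complications (the rate reported after training, in the Background) took 8 to 16 extra days, an assumption with no source in the article. T-test power then drops to between about 51% and 22%. That is an objection to the SD, not to the choice of test.
- **That Mann-Whitney would protect the trial in that case.** It does better than the t test, but its simulated power was only about 45% to 72%, depending on the base shape.
- **That the board sees unblinded data.** The article does not say so. Coded arms are enough to compare variances, and no comparison of effect is described.
- **That 108 is a miscalculation.** It is not.

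**Conclusion.** The point holds and should be fixed; it does not threaten the validity of the trial. The primary test is not fixed in advance, and the two checks that bear on it can conflict. The figure of 108 rests on an efficiency for normal data and is used when normality is doubted. It is therefore neither the likely need (102, if times are right-skewed) nor a safe bound (118 to 120).

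The practical size is modest. Under the plan's SD, Mann-Whitney gains about 6 to 10 percentage points of power over the t test if times are gamma or lognormal, and loses about 1 if they are normal. The choice of test changes the verdict on significance in about 5% to 11% of simulated trials. These figures assume the plan's means, an SD of about 3, 15% crossover and the shapes named. The disagreement rates between the checks also depend on thresholds that the article does not state.

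**What to change.** Amend the two statistical sections as follows:
1. Name Mann-Whitney as the test of the primary outcome, reported with a Hodges-Lehmann difference in days and its 95% confidence interval.
2. Exempt the primary outcome from the visual and Kolmogorov-Smirnov check.
3. Remove the judgement on the test after 75 patients. The board's safety reviews are not affected.
4. Delete the increase to 108 and keep 102, stating that its power assumes an SD of about 3 days.

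The cost is wording only, and up to 6 fewer patients are needed. The price is about 1 percentage point of power if the data prove exactly normal (about 2 in a separate run at 36 per arm without crossover: 80% against 78%). The Trial status section reports 78 of 102 patients randomized at submission, so the amendment should be dated before anyone compares recovery times between the arms.
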